## Methods/design

### Trial design

The design of the present study protocol is a double-blind, placebo-controlled randomized clinical trial.

After being randomly allocated, the experimental group will receive 20 min of active 2-mA tDCS once a day for 10 consecutive weekdays. The control group will receive a sham stimulation (placebo); the chosen parameters are that, after 40 s of real stimulation (2 mA), only a small current pulse occurs every 550 ms (110 mA over 15 ms) through the remainder of the 20-min period.

Neuropsychological and psychiatric assessments will be performed at the time of consent (baseline) and at 1 and 3 months following the end of the intervention (maintenance effect). The primary outcome will be cognitive function; the secondary outcomes will be the positive and negative symptoms. Outcome assessments will be performed by trial research staff. Primary and secondary outcome assessors (neuropsychologists and psychiatrists) and patients will be blinded to randomized allocation after assignment to the interventions.

The present study protocol was written in compliance with the Standard Protocol Items: Recommendations for Interventional Trials (SPIRIT) 2013 [9]. A completed SPIRIT checklist is available as a supplement (Additional file 1), and the schedule of this study is presented in Fig. 1. The study flowchart is shown in Fig. 2.

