### Power and sample size calculation

The sample size calculation was performed by using the *T* statistic and non-centrality parameter. The expected effect size of 0.8 was conservatively estimated on the basis of the results of more recently published studies [10]. The basis of the sample size estimation is an expected cognitive improvement of about 35% in the tDCS intervention group. The sample size was calculated assuming an aimed power of 80% and a standard deviation of the outcome in the population of 1.0 (standard normal deviate for α = Zα = 1.95996; standard normal deviate for β = Zβ = 0.84162). After consideration of a non-adherence rate of 10% and a drop-out rate of 10% in both arms, the case number results in 70 patients (35 patients per group).

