### Statistical analyses

The data will be analyzed with the Statistical Package for Social Sciences (SPSS 18.0, Chicago, IL, USA). Statistical significance will be set at *p* < 0.05 (two-tailed) for all analyses.

Student’s *t* test will be used in comparisons involving continuous clinical and sociodemographic variables with normal distribution and the Mann-Whitney test for comparisons involving clinical and sociodemographic data with non-normal distribution. Comparisons involving categorical variables will be performed using the chi-square test.

Analysis of Covariance (ANCOVA) with repeated measures, with intervention group used as intersubject factor, neuropsychological scores from MCCB tests as intrasubject factors, and years of education as a covariate, will be performed to evaluate the efficacy of intervention in the treatment of cognitive deficits (primary outcome). The same analysis, using PANSS negative and positive subscale scores as intrasubject factors and duration of illness as a covariate, will be performed to evaluate the efficacy of intervention in the treatment of negative and positive symptoms (primary outcome).

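### The MCCB and PANSS efficacy models name education or illness duration as covariate, not the baseline value of the analysed score; the precision lost runs from modest to large, depending on the contrast tested

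*Protocol article*

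**What the plan says.** Under Statistical analyses, the cognitive outcome is to be analysed by ANCOVA with repeated measures. Intervention group is the between-subject factor, the MCCB test scores are the within-subject factors, and there is one covariate: "years of education as a covariate, will be performed to evaluate the efficacy of intervention in the treatment of cognitive deficits (primary outcome"). The symptom model is the same analysis "using PANSS negative and positive subscale scores as intrasubject factors and duration of illness as a covariate". Tests are "two-tailed) for all analyses" at 0.05.

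The baseline values of both instruments will be available. Trial design states: "Neuropsychological and psychiatric assessments will be performed at the time of consent (baseline"), and again 1 and 3 months after the end of the intervention.

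The section names no visit or time factor. It does not say whether the baseline score is a level of the within-subject factor or sits outside the model, nor whether the group main effect or the group-by-time interaction is the efficacy test.

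**The concern.** A patient's own pre-treatment score is ordinarily the strongest available predictor of the same score at follow-up. The article does make a choice of covariate, and it chooses education for cognition and illness duration for symptoms. With 35 patients per arm, adjusting for the baseline value of the analysed score would reduce the standard error and remove the part of any chance baseline difference that carries through to follow-up. At stake is power: how much is given up, and whether that matters at a plausible effect size.

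**Working it through.** **The plan's own sample size first.** Power and sample size calculation gives "standard normal deviate for α = Zα = 1.95996", "standard normal deviate for β = Zβ = 0.84162", an effect size of 0.8 and a "standard deviation of the outcome in the population of 1.0". Per arm: 2 × ((1.95996 + 0.84162) / 0.8)² = 24.53, so 25. Treating 10% non-adherence as dilution of the effect (divide by 0.9²) and 10% drop-out as loss (divide by 0.9) gives 25 / 0.729 = 34.3, so 35 per arm and 70 in total. The stated figure reproduces, and it takes no credit for any covariate.

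**Assumptions not in the document.** The correlation r between visits is taken as 0.5, 0.7 and 0.8, equal for every pair of visits (compound symmetry). The treatment effect δ is equal at 1 and 3 months. Evaluable patients are 35 × 0.8 = 28 per arm, which counts both 10% allowances as losses. The main illustration uses δ = 0.5 SD; the planned 0.8 follows. The contribution of education or illness duration is ignored throughout.

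**Variance of each candidate contrast**, with SD = 1 and scaled so that each estimates δ:

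- Mean of two follow-ups, baseline-adjusted: (1 + r)/2 − r² = (1 − r)(1 + 2r)/2
- Mean of two follow-ups minus baseline (change contrast): 3(1 − r)/2
- Mean of two follow-ups, baseline unused: (1 + r)/2
- Group main effect over three visits: the effect is diluted to 2δ/3 and the variance is (1 + 2r)/3, so the effective variance is 3(1 + 2r)/4

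**Excess variance relative to the baseline-adjusted analysis** at r = 0.5 / 0.7 / 0.8:

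- Change contrast: 3/(1 + 2r) = 1.50 / 1.25 / 1.15
- Follow-ups only: (1 + r)/((1 − r)(1 + 2r)) = 1.50 / 2.36 / 3.46
- Main effect over three visits: 1.5/(1 − r) = 3.0 / 5.0 / 7.5

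**Power.** The noncentrality is λ = (28/2) × δ² / V. At δ = 0.5 this is 3.5/V. For r = 0.7, λ is 3.5/0.36 = 9.72 (adjusted), 3.5/0.45 = 7.78 (change), 3.5/0.85 = 4.12 (follow-ups only) and 3.5/1.80 = 1.94 (main effect). The group-by-visit test has the same λ as the change contrast but spends 2 numerator df. Denominator df are 53 for the adjusted test, 108 for the 2-df test and 54 for the others. Noncentral F gives:

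| Test (δ = 0.5 SD, 28 per arm) | r = 0.5 | r = 0.7 | r = 0.8 |
|---|---|---|---|
| Baseline-adjusted mean of follow-ups | 74% | 86% | 95% |
| Change contrast, 1 df | 56% | 78% | 92% |
| Group-by-visit, baseline as a level, 2 df | 46% | 69% | 86% |
| Follow-ups only, baseline unused | 56% | 51% | 49% |
| Group main effect over three visits | 32% | 28% | 26% |

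**At the planned effect of 0.8 SD**, for r = 0.5 / 0.7 / 0.8, the 2-df group-by-visit test has 87% / 98% / 99.9%, follow-ups only 92% / 89% / 87%, and the main effect over three visits 67% / 59% / 56%. Only the last falls below the 80% target.

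**The case against.** The strongest defence is that the model is a repeated-measures one and the visits are baseline, 1 month and 3 months, so baseline may well be one of the repeated levels. A group-by-time test is then a change-type contrast. It differences out a chance baseline imbalance, apart from regression to the mean, and recovers most of the baseline information when r is high. That stands, and it rules out several stronger statements that a reader might infer.

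- **That much of the available precision is certainly lost.** Under a group-by-time test the excess variance is 25% at r = 0.7 and 15% at r = 0.8. The text does not exclude this reading.
- **That chance imbalance passes straight into the estimate.** This holds only if baseline is left out or the group main effect is tested.
- **That baseline adjustment lifts power from 45% to 56%, 73% or 87%.** Those figures (0.5 SD, 28 per arm) set a single-visit adjusted comparison against an unadjusted two-sample t test. The article reserves t tests for clinical and sociodemographic comparisons; efficacy uses the repeated-measures model.
- **That the whole step from 69% to 86% at r = 0.7 is due to the covariate.** Going from 2 df to a 1-df change contrast accounts for 69% to 78%; the covariate accounts for 78% to 86%.
- **That the trial is undersized or biased.** The 70 reproduces without any covariate gain, and randomisation protects the comparison.

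The defence can also say that "The expected effect size of 0.8 was conservatively estimated on the basis of the results of more recently published studies" and that, at 0.8, group-by-time power already exceeds target. That is so for that contrast, but not for the main effect over three visits, and a smaller true effect would make the difference count. A full protocol or SAP may settle the time factor and contrast, so their absence here is not the complaint in itself. The choice of covariates is stated, and it leaves out the most useful one.

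**Conclusion.** The point holds as a recommendation on efficiency. The named covariates are education and duration of illness, the baseline value of the analysed score is collected but not used as a covariate, and using it is at least as precise under every reading of the model. The size is conditional. At 0.5 SD the gain in power over a 1-df change contrast is about 17, 8 and 3 percentage points at r = 0.5, 0.7 and 0.8. It is larger against the 2-df interaction (27, 17 and 9 points, part of it due to the df). It is large if baseline is left out (17, 35 and 46 points) or if the group main effect over three visits is the test (41 to 69 points). These figures rest on the assumed r, compound symmetry, an equal effect at both follow-ups and 28 evaluable per arm; the document supplies none of them. The case for high r and a group-by-time test is therefore a modest loss, not a serious one.

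**What to change.** In the primary model, use the 1- and 3-month scores as outcomes, add the baseline value of the same MCCB score as a covariate, and test the group effect at follow-up. This applies to whichever MCCB score is analysed; the article does not name a composite, and this change does not require one. In the symptom models, do the same with the baseline value of the PANSS positive or negative subscale. Education and duration of illness may stay as additional covariates. State this wording before unblinding; Trial status describes the trial as ongoing.

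The cost is about one degree of freedom and no new data. It is slightly more than adding a covariate, because it also moves baseline out of the outcome vector and fixes which contrast is tested. That settles the ambiguity on which the size of the loss depends.

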### Data monitoring

The trial is externally monitored (Laboratório Interdisciplinar de Neurociências Clínicas, Department of Psychiatry, Universidade Federal de São Paulo, Sao Paulo, Brazil) in accordance with Good Clinical Practice (GCP) recommendations.

### Confidentiality

Information about study subjects is kept confidential. All data are entered into a dedicated study data management system, and in all data documents study subjects are assigned an individual identifying code which does not contain identifying information.

## Discussion

Historically, psychiatric treatments have focused on attenuation of established symptoms, reductions of deficits, and health restoration, neglecting strategies related to promotion of competencies. Identification and correction of abnormalities associated with worse outcomes in early stages of disease have recently assumed an important role in an emerging preventive medicine, whose concepts have been gradually incorporated by psychiatry. In this sense, it is conceivable to hypothesize that rehabilitation of cognitive deficits in the early stages of schizophrenia might improve both clinical and functioning outcomes.

Cognitive deficits are core symptoms of schizophrenia and have been associated with marked impairment in global functioning [5]. Despite the unquestionable efficacy of antipsychotic drugs in the treatment of positive symptomatology, they have demonstrated no efficacy in treatment of other symptom dimensions, including cognitive deficits, which are present even before the beginning of disease [2, 21].

The development and utilization of potentially effective neuroenhancement tools such as non-invasive neuromodulation techniques for the treatment and rehabilitation of cognitive impairment in the early stages of schizophrenia may contribute to improve outcomes of disorder and eventually further our understanding of the nature of the complex and dynamic neural processes underlying those abnormalities. Transcranial direct current stimulation has proven to be safe and efficacious as a cognitive enhancement strategy for healthy subjects [7, 10]. Additionally, increasing evidence has suggested that tDCS is potentially helpful in the treatment of different symptom dimensions in schizophrenia, including cognitive deficits [6].

### Trial status

The Protocol Version is 2.0. The trial is registered at ClinicalTrials.gov with identifier number NCT03071484.

Secondary identifying numbers include the Universal Trial Number (UTN) U1111-1217-4425; ReBec (Registro Brasileiro de Ensaios Clínicos) - Brazilian Clinical Trials Registry RBR-2T3HFV.

This trial is currently ongoing. The recruitment of subjects is expected to finish in 2019.

## Abbreviations

IQ: Intelligence quotient (IQ)
MATRICS: Measurement and Treatment Research to Improve Cognition in Schizophrenia
MCCB: MATRICS Consensus Cognitive Battery
PANSS: Positive and Negative Syndrome Scale
PSP: Personal and Social Performance Scale
SCID-5: Structured Clinical Interview for Diagnostic and Statistical Manual of Mental Disorders, 5th edition
tDCS: Transcranial direct current stimulation
WAIS-III: Wechsler Adult Intelligence Scale Third Edition
